### Sample size

There is so far still no definite sample size calculation for fMRI research; however, as a result of previous fMRI studies, there should be at least 10 participants in each group to obtain brain imaging with statistical significance [18]. Combining the preceding clinical trial experiences all over the world recently with the withdrawal rate, we plan to enroll a total of 40 participants with 20 patients in each group.

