#### fMRI data processing

Functional MRI data will be processed by statistical parametric mapping (SPM8) of MATLAB2009b, DPARSF, and Freesurfer (http://surfer.nmr.mgh.harvard.edu/) software packages. Original data will be corrected; physiological artifacts, slice timing, affine head motion, and nonbrain extraction will also be implemented. Moreover, spatial smoothing and temporal filtering will be applied. Cortical surface reconstruction will be performed to improve structural–functional coregistration using FreeSurfer’s register tool (http://surfer.nmr.mgh.harvard.edu/), and then the cortex thickness will be calculated. The cortex thickness, superficial area, and volumetric of every group will be compared using a paired *t* test (*p* < 0.001, cluster size > 100 vertices). The cortex thickness, the local consistency changes of the brain region, and clinical outcomes with significant statistical differences will be analyzed by multiple regression analysis. Then we will acquire the brain regions correlated with an acupuncture clinical effect via analyzing the correlation index values *R* and *P* with the change of cortex thickness, ReHo of brain region, and clinical outcomes.

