### Statistical analysis

In this study, statistical analysis will be performed by a professional statistician blinded to the whole trial process using SPSS19.0 statistical software, and based on the intention-to-treat principal and preprotocol population. All demographic, baseline characteristics, curative effects, and fMRI images of the subjects will be analyzed with different approaches.

In terms of the data description, the enumeration data/quantitative data will be expressed with/as a percentage or proportion, while the measurement data/qualitative data will be represented as average and standard deviation. On this occasion of normal distribution and homoscedasticity, one-way analysis of variance (ANOVA) will be applied to identify differences in measurement data/qualitative data of comparison. Other covariates will be considered for further revision and if necessary stated in the statistical analysis project prior to data lock. Similar analysis of covariance (ANCOVA) models will used for secondary analysis to adjust baseline characteristics. A *q* test (Newman–Keuls) will be used for pairwise comparison. In case of nonnormally distributed data and heteroscedasticity data, a nonparametric test (Kruskal–Wallis *H* test) will be performed, and a rank sum test (Nemenyi) will be conducted to identify difference between groups. The enumeration data/quantitative data will be compared by chi-square test, while classification data will be evaluated with a rank sum test. In addition, the exploratory analysis will be implemented to describe group means over time. A two-sided test will be applied for available data and *p* < 0.05 will be taken as significant for each outcome. Missing data will be explored and if necessary multiple imputations will be utilized.

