There are also some accessed findings about several brain regions which are concerned with emotional problems. Previous studies suggested that the cerebral limbic system and the surrounding structure are the brain regions which are strongly linked with the affective state, as well as adjusted by frontal lobe, temporal cortex, and subcortex. Recent neuroimaging studies have implicated that several brain regions, including the orbitofrontal cortex (OFC), ventral medial prefrontal cortex (vmPFG), amygdale, hypothalamus, brainstem, cingulated cortex, thalamus, hippocampus, sensory cortex, and so on, play a key role in emotional regulation [44–46]. Meanwhile, other studies investigating the plasticity of emotional neurocircuitry and mood disorders also provide substantial support for the viewpoint that some brain regions, such as the prefrontal cortex, amygdale, hippocampus, and thalamus, are the critical sections of emotional neurocircuitry and exert an important effect on emotional regulation [47, 48]. Sleep disturbances may contribute to the weakened emotional regulation of the prefrontal cortex. Long-term insomniacs tend to build an inner emotion mechanism to relieve the stress of insomnia [49]. Moreover, findings of a cerebral functional imaging study declared that when the subcortex and autonomic nerve system are inhibited by the prefrontal cortex, a bad affective state including anxiety and depression will be generated [50, 51]. Some research considered that the amygdale may impact the plasticity of the hippocampus and thalamus [52, 53], whereas its plasticity is also influenced by regulation of the prefrontal cortex, which will inhibit negative emotion by connecting with the amygdale [54]. Given that the amygdale may be closely related with sleep disorder, previous studies revealed that when a primary insomnia patient turns to a sleep state from waking status there are abnormal activity brain regions including the amygdale, hippocampus, thalamus, and prefrontal cortex [55, 56]. Based on the possibility that the acupuncture signal may stimulate the central integration neural signal and improve emotional disorder, and the findings that there may be abnormal nerve function in the emotional neurocircuitry of insomniacs, it is hypothesized that the emotional neurocircuitry and emotional center cortex may integrate and respond to the acupuncture signal; during this procedure, central regulation of the prefrontal cortex and functional connection of the amygdale may play an important role. Thus, after the sleep-related center responded/answered acupuncture signal, positive regulation of the sleep architecture and mood disorder is able to improve sleep difficulties.

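### The fixed 100-vertex cluster rule is tied to no corrected error rate, and brain regions are then picked by uncorrected R and P

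*Protocol article*

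**What the plan says.** All the imaging rules are in the protocol article, section fMRI data processing.

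- Structural change: "The cortex thickness, superficial area, and volumetric of every group will be compared using a paired" t test, at p < 0.001 and "cluster size > 100 vertices". No family-wise or false-discovery level accompanies this rule.
- Smoothing: "spatial smoothing and temporal filtering will be applied", with no link between the smoothing and the 100-vertex extent.
- Regression: cortical thickness, local-consistency changes and "clinical outcomes with significant statistical differences will be analyzed by multiple regression analysis".
- Region finding: "Then we will acquire the brain regions correlated with an acupuncture clinical effect via analyzing the correlation index values" R and P, relating change in thickness and ReHo to clinical outcomes. No correction over regions or outcomes is stated.

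The Statistical analysis section sets two-sided p < 0.05, which "will be taken as significant for each outcome", and names no correction for imaging. Under Sample size, "we plan to enroll a total of 40 participants with 20 patients in each group". PSQI is the primary outcome, but the Hypothesis section includes a between-group difference on fMRI, and the Discussion expects the results to verify a central mechanism.

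**The concern.** A cluster-extent threshold controls the chance of a false cluster only in relation to how smooth the map is. A count of 100 vertices is a large cluster on a rough map and a small one on a smooth map, so the same written rule can be strict or lax.

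The next step searches for regions whose change correlates with clinical change and takes those that stand out on R and P. With few patients and many candidate regions, such a search finds correlations when none exist. It also overstates the size of those that do exist, because only large sample values pass.

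At stake is the trial's mechanism claim: which brain regions change, and which of them go with clinical improvement.

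**Working it through.** The plan gives no imaging error rate to reproduce, so the check asks what its stated rules deliver.

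**1. The cluster rule**

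Inputs from the protocol article: p < 0.001 (two-sided), extent over 100 vertices, 20 patients per group. Assumptions: map size, smoothing, and a flat grid of Gaussian-smoothed noise standing in for the cortical surface. Each map is a one-sample t map of null paired changes, and a hit is any cluster above 100 points.

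The last column gives the extent relative to one smoothness element, 100 / FWHM², with FWHM (the smoothing width) in vertex spacings.

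| Map size (points) | FWHM (spacings) | Maps run | Chance of a false cluster | 100 / FWHM² |
|---|---|---|---|---|
| 102,400 | 5 | 150 | 0% | 4.0 |
| 102,400 | 10 | 150 | 1% | 1.0 |
| 102,400 | 15 | 150 | 13% | 0.44 |
| 102,400 | 20 | 150 | 27% | 0.25 |
| 102,400 | 25 | 150 | 33% | 0.16 |
| 160,000 | 5 mm / 0.64 mm = 7.8 | 60 | 0% | 1.6 |
| 160,000 | 10 mm / 0.64 mm = 15.6 | 834 | 23% | 0.41 |
| 160,000 | 15 mm / 0.64 mm = 23.4 | 60 | 25% | 0.18 |

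Monte Carlo error is moderate: for 33% of 150 maps the standard error is √(0.33 × 0.67 / 150) = 0.04, and for 25% of 60 maps it is √(0.25 × 0.75 / 60) = 0.06. Both map sizes show the same pattern: below 5% when the extent covers at least about one smoothness element, well above 5% when it covers less than half of one. These rates are per map. The rule is applied to 3 measures × 2 groups = 6 comparisons, or 12 maps if hemispheres are analysed separately.

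**2. The correlation search**

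Assumptions: correlations run within one arm of 20, the general 0.05 level applies, and regions are independent.

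- Smallest significant correlation: r = t / √(n − 2 + t²). With n = 20 and t(0.975, 18) = 2.101, r = 2.101 / √(18 + 4.414) = 0.444. If both arms were pooled (n = 40) it would be 0.312.
- Chance of at least one p < 0.05 with no true correlation: 1 − 0.95^K. This is 0.23 for K = 5, 0.40 for K = 10, 0.64 for K = 20 and 0.92 for K = 50. The mean largest |r| in simulation was 0.36, 0.42, 0.48 and 0.55.
- Overstatement: with a true correlation of 0.3, the simulated correlations that reached p < 0.05 averaged 0.54.

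**3. The entry filter**

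This step was checked separately. The variable was required to show a within-arm paired change at p < 0.001 (n = 20, assumed mean changes of 0.3 and 0.8 SD) before being correlated.

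- True correlation 0: mean |r| was 0.186 without the filter and 0.185–0.186 with it. The false-positive rate stayed at 0.05.
- True correlation 0.3: mean r fell from 0.293 to 0.234–0.271.

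So a filter on within-group change does not inflate r; the overstatement comes from selecting on R and P. The filter does make the set of outcomes analysed depend on the results.

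**The case against.** The best defence is that an article condenses a fuller plan. The kernel width, cluster-correction settings and region list may be fixed there, and their absence here is no fault. That stands. It does not answer the point, because the article commits to a specific extent and a specific way of finding regions.

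It is also fair that p < 0.001 plus an extent limit gives real protection, and that imaging is neither the primary nor a listed secondary outcome. Both limit the weight of the point.

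Several stronger readings are tempting, but the document does not support them:

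- **The significance filter inflates the correlations.** For within-group change, which is the comparison the section describes, step 3 shows it does not. Inflation could arise if arms were pooled and both variables selected on between-arm differences, but pooling is not stated. Grammatically, the filter may also cover only the clinical outcomes.
- **Correlations are confined to the acupuncture arm.** The section does not say which patients enter, and both groups are scanned. The n = 20 figures are therefore conditional.
- **The subcortical regions in the Discussion cannot be tested.** The vertex rule is attached to thickness, area and volume only. ReHo also enters the brain-clinical analysis and is not limited to cortical vertices.
- **The Discussion's regions should have been the fixed targets.** The text is tentative: "central regulation of the prefrontal cortex and functional connection of the amygdale may play an important role". Making them targets is one design choice among several.
- **A false cluster somewhere is nearly certain.** Compounding 23.4% over 12 maps gives 1 − 0.766^12 = 0.96. That takes one assumed smoothing level and treats three measures of the same cortex as independent.

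**Conclusion.** The point holds in a limited form and should be acted on. The stated cluster rule does not fix an error rate. Under the assumed map sizes and smoothing, its false-cluster rate per null map at n = 20 runs from about 0% to about 25–33%, before several measures, hemispheres and groups are counted. The accurate description is that error is not shown to be controlled, since at light smoothing the rule can be conservative.

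The correlation search has no stated correction. Within one arm of 20 at p < 0.05, the chance of at least one false region rises from 0.23 over 5 independent regions to 0.92 over 50. The number of regions, their independence, the arm and the level are assumptions. The structural rule and the reliance on R and P are in the text.

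The primary PSQI comparison is untouched. What is affected is the strength of the mechanism claim.

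**What to change.** 1. Keep the p < 0.001 vertex threshold. Replace the fixed 100-vertex extent with cluster-wise family-wise error control at 0.05, by permutation or by Monte Carlo simulation at the data's own smoothness, corrected over hemispheres and measures.
2. Enter the clinical outcomes, at least PSQI change, in the brain-clinical analysis whether or not they are significant.
3. Apply Holm or FDR correction over all region-by-outcome correlations and report every one of them. Otherwise label them exploratory.

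The cost is some analysis time, with no new data or visits, and fewer regions will be declared significant. For example, under Holm over 50 correlations the first step is 0.05 / 50 = 0.001, so with 20 patients the largest correlation must exceed 0.68 rather than 0.44.

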## Methods/Design

### Objectives

The study aims to research the influence of acupuncture on perimenopausal insomniacs, such as determining the difference of brain activity and the relevance between the brain and clinical effects, as well as assessing the effect of acupuncture for perimenopausal insomnia.

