### Hypothesis

According to the validity of acupuncture on perimenopausal syndrome, insomnia, and emotional disorder, as well as the influence of acupuncture on brain function, we hypothesize that acupuncture will improve the symptoms of perimenopausal insomniacs, and there will be a difference between acupuncture and medicine control based on the fMRI examination.

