#### fMRI examination procedure

The MRI examination (Signa 3.0 T Magnetic Resonance Imaging Scan; GE General Electric Company) will be performed to collect brain images offering more visualized proof. The MRI protocol for this study consists of the following parameters: high-resolution three-dimensional T1 weighting brain volume (Bravo) sequence scanning: repetition time (TR) of 8.16 ms, echo time (TE) of 3.18 ms, flip angle 7°, 256 × 256 mm^2^ field of view (FOV), voxel size of 1 × 1 × 1 mm^3^, 180 sections of 1.0-mm thickness. Before scanning, the subjects will be requested to keep quiet and their eyes closed, especially not to think something and to avoid sleep. In order to ensure the participants stay awake, the researcher will inquire of the subject whether they are awake during and after the scanning procedure. Both of the intervention groups will be examined twice (before and after treatment).

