
Nevertheless, there are also limitations in this study. Concerning the unfeasible blinding to participants, one limitation is the possibility of a high risk of bias regarding blinding by unconcealed allocation. We therefore strictly conduct randomization and separate the acupuncturist, assessor, and statistician. Meanwhile, patients divided into the acupuncture intervention group may have more opportunities to make contact with their acupuncturists and establish a good doctor–patient relationship rather than those of the western medicine control group, which is likely to improve the therapeutic effect [57]. Hence, we will maintain close contact with patients in the control group by telephone, Internet, and so on, to minimize this potential bias.

In conclusion, the results of this trial are expected to confirm whether an acupuncture formula based on liver differentiation is effective in relieving perimenopausal insomnia. Combining neuroimaging with a neurophysiology method, the relevant outcomes are predicted to verify the central mechanism of acupuncture treatment. We believe that the results will exert a positive effect on acupuncture treatment for perimenopausal insomnia (Additional files 1 and 2).

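### The brain–clinical correlation that is to name regions of an acupuncture effect makes no use of the estazolam arm, so it can show association with symptom change but not an acupuncture mechanism

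*Protocol article*

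**What the plan says.** All references are to the protocol article.

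- **fMRI data processing** sets out a chain of three steps. First, cortical measures: "volumetric of every group will be compared using a paired" *t* test, with p < 0.001 and clusters above 100 vertices. Second, cortical thickness, local consistency and "clinical outcomes with significant statistical differences will be analyzed by multiple regression analysis". Third: "Then we will acquire the brain regions correlated with an acupuncture clinical effect via analyzing the correlation index values" R and P, taken between change in cortical thickness or ReHo and the clinical outcomes.
- **fMRI examination procedure** has both arms scanned before and after treatment.
- **Hypothesis** states that "there will be a difference between acupuncture and medicine control based on the fMRI examination".
- **Objectives** include "determining the difference of brain activity and the relevance between the brain and clinical effects".
- **Discussion** concludes that "the relevant outcomes are predicted to verify the central mechanism of acupuncture treatment".
- **Sample size**: "we plan to enroll a total of 40 participants with 20 patients in each group".

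The **Statistical analysis** section offers ANOVA and, secondarily, ANCOVA for comparing groups. It does not connect either to the brain–clinical step.

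**The concern.** The rule names a region as belonging to the clinical effect of acupuncture from R and P. The null behind that P is that brain change and clinical change are unrelated. It is false whenever patients who sleep better, for whatever reason, also show a change in the region: natural course, expectation, contact with the therapist, or a pathway shared with estazolam. Rejecting it says nothing about which treatment, if any, produced the change.

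To attribute the region to acupuncture relative to the comparator, one of two things has to differ between arms: the brain change itself, or its relation to the clinical change. The rule as stated uses neither, and the only imaging test before it is a paired one within each group.

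At stake is the mechanistic conclusion, which the Discussion presents as a main purpose of the trial. The difficulty is separate from multiplicity and region selection, since it remains for a single region chosen in advance.

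**Working it through.** The documents give no brain–symptom correlation, effect size or SD, so there is no planned figure to reproduce for this step. All correlations (ρ) and shifts below are assumptions.

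**Inputs from the article.** 20 per arm; two-sided 0.05 (Statistical analysis); p < 0.001 is stated only for the paired imaging comparison.

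**1. How often R is significant when nothing differs between arms.** One region, one outcome, the same bivariate normal distribution in both arms, 20,000 simulated trials.

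| assumed ρ | acupuncture arm, n = 20 | both arms pooled, n = 40 | arm × brain-change interaction |
|---|---|---|---|
| 0 | 5% | 5% | 5% |
| 0.3 | 26% | 49% | 5% |
| 0.4 | 43% | 74% | 5% |
| 0.5 | 65% | 92% | 5% |
| 0.6 | 83% | 99% | 5% |
| 0.7 | 96% | 100% | 5% |

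A between-arm *t* test of brain change also stays at about 5% throughout.

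Hand check by Fisher's z, power ≈ Φ(atanh(ρ)·√(n − 3) − 1.96). For ρ = 0.5 and n = 20: 0.549 × √17 = 2.265, and Φ(0.305) = 0.62, close to the simulated 65%. For ρ = 0.5 and n = 40: 0.549 × √37 = 3.341, and Φ(1.381) = 0.92.

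**2. Effect of the threshold and the filter.** With p < 0.001 applied to the acupuncture-arm correlation, the rates at ρ = 0.3, 0.4, 0.5 and 0.6 fall to 2%, 5%, 13% and 31%. The condition on significant differences in the regression step can be read in two ways. In both, an assumed non-specific change of 1 SD occurs in both arms, and the correlation is tested at 0.05.

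| reading of the filter | ρ = 0.3 | ρ = 0.5 | ρ = 0.7 |
|---|---|---|---|
| before–after (brain p < 0.001, outcome p < 0.05), then significant R | 17% | 42% | 66% |
| between-arm clinical difference, then significant R | 1.1% | 2.8% | 4.7% |
| significant R among trials that pass the between-arm filter | 22% | 57% | 94% |

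The before–after reading is the natural one, because the paired test is the only imaging test named. A between-arm clinical filter would make false labels rare, but the correlation that follows it still does not test whether the region is specific to acupuncture.

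**3. Pooling without an arm term.** If the arms differ by d SD on average in both variables and there is no relation within patients, the pooled correlation is about (d²/4)/(1 + d²/4). For d = 0.8, 1.0 and 1.5 that is 0.14, 0.20 and 0.36. With 3,000 simulated trials, the pooled R is significant in 14%, 24% and 66%, while an arm-adjusted slope stays at about 5%.

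**4. Which arm contrast is needed.** Suppose a true mediator: slope 0.6 in both arms, with acupuncture shifting the region by 1 SD. The slopes are equal, so the interaction rejects in only about 5% of trials. The between-arm contrast of brain change has non-centrality 1/√(2/20) = 3.16 on 38 degrees of freedom (critical value 2.02), which gives 87% power. Where the slopes do differ, the interaction has about 35% power for 0.5 versus 0, 49% for 0.6 versus 0 and 65% for 0.7 versus 0. It rejects just as often (49%) when the slope of 0.6 is in the estazolam arm and that of acupuncture is 0, so its direction must be read as well.

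**The case against.** **The percentages are power, not error.** This stands. They are the chance of detecting an association that was assumed, and the test is valid for association. One stated objective is indeed a relation between brain and clinical effects. A reader might infer that the plan mislabels regions in 26% to 83% of cases. The documents do not support that as a property of the plan: they give no ρ, the figures in the first table ignore the filter, and at ρ = 0 without an arm difference the test holds 5%.

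**Pooling is not stated.** This also stands. The wording points rather to the acupuncture arm, so the pooled figures warn against one possible implementation.

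**A reader might infer that only an arm-by-change interaction would do.** That is wrong: step 4 shows that it would miss about 95% of genuine mediators with equal slopes. Nor does equality between arms show that acupuncture does nothing, because estazolam is active and both treatments may act through the same region.

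**Regression terms belong to an analysis plan that is not shown.** This stands in part. The article lists no regressors and defers covariates. But it does state the statistic, the label taken from it and the conclusion expected. That is a rule with its inference, not an omitted detail. The Background and Hypothesis sections promise a comparison with medicine that this rule does not make.

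**Imaging is neither the primary nor a listed secondary outcome.** True, and it limits the reach of the point. The article nevertheless does not call the analysis exploratory, and presents mechanism as a main purpose.

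**Conclusion.** The point holds as one about inference. As written, R and P can show that brain change goes with symptom change. They cannot attribute a region to acupuncture rather than to sleeping better in general, and they cannot verify a central mechanism of acupuncture.

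This conclusion does not depend on any assumed ρ. How often a general correlate would be labelled as acupuncture-related does: from 5% at ρ = 0 to 83% at ρ = 0.6 without a filter, 17% to 66% for ρ = 0.3 to 0.7 under the before–after filter, and 1% to 5% under a between-arm clinical filter. These figures hold for one region, one outcome, normal data and no withdrawals.

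The change should be made before the data are analysed. The primary PSQI comparison and any efficacy conclusion from it are unaffected.

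**What to change.** 1. Compare the change in cortical thickness and ReHo between arms, adjusted for the baseline value, with confidence intervals. This is the contrast that the Hypothesis section calls for.
2. Fit the brain–clinical regression over both arms with an arm term, and do not use a pooled correlation without it. Report the arm-by-brain-change interaction as supplementary, with its confidence interval, direction and low power stated, and not as the sole criterion.
3. Describe a region as related to acupuncture relative to estazolam only if a between-arm contrast (brain change or slope) supports it. Otherwise call it a correlate of sleep improvement.
4. Reword the last step under fMRI data processing and the concluding paragraph of the Discussion as exploratory association. Add that an active, unblinded comparator cannot rule out expectation or contact effects; the Discussion already acknowledges the lack of blinding and the unequal contact.

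The cost is wording and a few model terms, with no new patients, scans or data. The downside is that fewer regions can be claimed as specific to acupuncture.
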